### Study population

This study comprises nine hospitals in the Netherlands: two academic, four tertiary teaching, and three regional hospitals, with 200 to up to more than 1,300 beds each. Eight hospitals have a NIAZ accreditation. This accreditation of the Dutch Institute for Health Care Accreditation (NIAZ, part of the International Society for Quality in Healthcare) is provided to hospitals that meet international standards developed and tested for external evaluation of health-care organizations [23]. Two hospitals are part of the Dutch Federation of University Medical Centers (NFU) and provide the most specialized care [24]. Four hospitals are part of the Association of Tertiary Medical Teaching Hospitals (STZ) and provide highly specialized medical care (the next level of specialization below that of NFU hospitals) [25]. Although the hospitals are not randomly chosen, the stratification in three classes is a strong point, and we believe these hospitals represent the practice of Dutch hospital care. Within these clusters, we assess 1,800 surgical patients distributed over four measurement points, i.e., 450 patients per measurement point with 50 patients per hospital (see the “Power calculation” section below). The study focuses on patients undergoing elective abdominal or vascular surgery with a mortality risk ≥1% [10]. These surgeries are selected because of the estimated higher risk of complications and hospital mortality, as the number of included surgical patients is otherwise too small to be able to find significant effects of guideline adherence on perioperative patient safety (second research question). Exclusion criteria are the following: 1) patients younger than 18 years, 2) patients in day care (1-day hospital stays are defined as hospital admissions of 24 h or less), 3) patients undergoing cardiac surgery, 4) patients undergoing organ transplantations (except kidney transplants), and 5) patients undergoing emergency surgery, i.e., surgery needed within 24 h and/or without an pre-anesthesia evaluation record available and/or surgery with a start time after 4.59 PM or before 7.30 AM or during the weekend. Key disciplines are also involved as study objects: surgeons, anesthesiologists, OR, anesthesia, recovery, and ward nurses, and ICU employees.

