### Data sources

Information about the processes and outcomes of perioperative care are retrospectively derived from patient medical records in the participating hospitals by two researchers (YE and GB). The first 50 patients undergoing an initial elective surgery within the measurement period and who meet the inclusion criteria are selected from the hospital databases.

To measure the structure indicators of the national indicator set, the contact person in each hospital is invited to fill out a short questionnaire on the underlying items of the structure indicators on a dichotomous scale (yes/no).

Health-care providers in the concerning hospitals are invited to respond to two different questionnaires and additional background questions on gender, medical position, and years of experience in the current function and in the current hospital. The Team Climate Inventory (TCI) [33] and the Hospital Survey on Patient Safety Culture (HSOPS) [34] are used to analyze whether team climate and patient safety culture are determinants of guideline adherence. The TCI measures the climate of the various teams of health-care providers. Good team work is essential to provide proper and safe care [35-37]. The TCI is a valid, reliable, and discriminating self-report measure of the climate of a hospital team. The TCI is based on a four-factor theory of team climate for innovation and assesses the factors, vision, participative safety, task orientation, and support for innovation in 13 subscales [33]. To measure the patient safety culture, we use the HSOPS [34,38]. The HSOPS is a valid and reliable survey for assessing the patient safety culture in hospitals. It measures 12 dimensions of patient safety culture on the basis of ideas of unsafely designed care processes or systems that increase the likelihood of the occurrence of adverse events.

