### Analysis

After each measurement period, data are manually checked to identify out-of-range answers, inconsistent or missing data. Because of the hierarchical design (patients nested within hospitals), multilevel linear and logistic regression analysis will be used to compare the outcomes between treatment groups, with age, sex, the American Society of Anesthesiologists (ASA) physical status classification, and socioeconomic status (SES) as covariates. The ASA physical status classification is a five-point scale ranging from ASA 1 (healthy patient) to ASA 5 (moribund patient not expected to survive without surgery, e.g., a patient with a ruptured aortic aneurysm) [41]. Time will be included as fixed effect [22]. The association between guideline adherence and patient outcomes will also be analyzed to determine whether better adherence leads to better patient outcomes. We will use SPSS version 20.0 for data analysis. Significance for all analyses will be set at *P* < 0.05.

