The generalizability of the findings will be high because the study is carried out in a large, heterogeneous sample of nine hospitals across the country. A further strength of this study is the wide scope; we perform measurements at the cluster level and the level of their individual members, i.e., care providers and patients. A questionnaire is sent to the key disciplines to explore all relevant barriers and facilitators to guideline adherence and opportunities for improvement. A better understanding of the barriers and facilitators and a strategy tailored to local circumstances will enhance the implementation of the perioperative guidelines like already mentioned [55,53]. We also carry out a process evaluation to analyze the mechanisms and processes responsible for the outcomes of the effect evaluation; a causal relationship between implementation activities and change in outcomes is difficult to identify because of the presence of confounding factors, like local hospital initiatives to improve patient safety. In case of a multifaceted implementation strategy, the process evaluation is especially important to specify which intervention was most effective [53]. Insight into the implementation process is also relevant for other hospitals that can benefit from the lessons learned. To improve the internal validity, the following actions will be undertaken. To reduce selection bias, the first 50 patients that meet the inclusion criteria are selected from the hospital databases in all hospitals at each measurement point. A possible limitation of the survey investigations is response bias, which will be minimized by sending reminders. Information bias is reduced by having the same researchers (YE and GB) checking the data from the hospital registries and medical records. An independent researcher checks the data entries. An independent statistician will check the analyses. To prevent confounding bias, we study potentially confounding determinants, such as team climate and patient safety culture. To prevent publication bias, the study has been registered in the Dutch register for clinical trials. Additionally, we have installed an external advisory board with the special tasks of checking the design and the integrity of the study and giving feedback.

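### The patient-level models leave out type of surgery, although eligibility turns on it; adding it is nearly free and would bring a modest gain in precision and protection against confounding

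*Protocol article*

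**What the plan says.** The Analysis section of the protocol article states that "multilevel linear and logistic regression analysis will be used to compare the outcomes between treatment groups". The adjustment set it names is age, sex, ASA class and "socioeconomic status (SES) as covariates". On the measurement rounds it adds: "Time will be included as fixed effect". The same section plans an analysis of the association between adherence and patient outcomes and gives no separate adjustment set for it.

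Under Study population, eligibility rests on the operation: "The study focuses on patients undergoing elective abdominal or vascular surgery with a mortality risk ≥1" (per cent). The article explains that these operations were chosen for their higher expected risk of complications and death. Data sources says how each round is filled: "The first 50 patients undergoing an initial elective surgery within the measurement period". The Discussion repeats this ("the first 50 patients that meet the inclusion criteria are selected from the hospital databases in all hospitals at each measurement point"). No quota or stratification by procedure is described. The data are "retrospectively derived from patient medical records in the participating hospitals".

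The matching of hospital groups is described by hospital type and location. The confounders named under Process evaluation and in the Discussion are team climate, safety culture, local initiatives, other audits and studies, registration systems and mergers. Surgical mix is not among them.

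**The concern.** The article treats the kind of operation as a driver of complications and mortality when it selects patients, then omits it from the models for those outcomes. ASA class grades the patient's condition, not the procedure.

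The hospital effect largely removes a hospital's average mix, and the fixed time effect removes a shift shared by all nine hospitals. A change in the mix of one hospital, or one group of hospitals, between rounds is left. With only three randomised groups, such changes need not cancel. If risk differs by type of operation, part of the change would be credited to or taken from the intervention, and some explainable outcome variation would stay in the residual.

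The adherence-outcome analysis is more exposed. It is a non-randomised comparison. If type of surgery affects both adherence and complications, it confounds that association without any change in mix between rounds.

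**Working it through.** **Inputs from the article.** Nine hospitals in three groups of three, four measurements, the Table 1 layout, 50 patients per hospital and round, ICC 0.1-0.3, alpha 0.05 (two-sided assumed), adherence rising from 50% to 65%, stated power at least 0.85.

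**Assumptions, because the article gives no figures.** Outcome risk p = 20%; vascular share q = 30-50%; risk difference between surgery types g = 10, 20 or 30 points.

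**1. The plan's own figure.** The Hussey and Hughes variance is

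Var = Iσ²(σ² + Tτ²) / [(IU − W)σ² + (U² + ITU − TW − IV)τ²],

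where σ² is the variance of a hospital-round mean. Table 1 gives I = 9, T = 4, U = 18, W = 126, V = 42, so the two brackets are 36 and 90. With σ² = 0.25/50 = 0.005 and, at ICC 0.1, τ² = (0.1/0.9) × 0.25 = 0.0278:

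Var = 9 × 0.005 × (0.005 + 0.1111) / (36 × 0.005 + 90 × 0.0278) = 0.00195, SE = 0.0442.

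Power = Φ(0.15/0.0442 − 1.96) = 0.925. At ICC 0.2 and 0.3 it is 0.921 and 0.920. The stated minimum of 0.85 is met. That calculation neither assumes nor excludes adjustment for surgery type.

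**2. SE for an outcome with 20% risk, ICC 0.1.** Scaling gives 0.0442 × √(0.16/0.25) = 0.035. If 0.16 is read as total variance, so that the residual part is 0.9 × 0.16, the SE is 0.035 × √0.9 = 0.034. Hence 3.4-3.5 points.

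**3. Chance change in mix.** In one hospital-round the SD of the share is √(0.3 × 0.7/50) = 6.5 points to √(0.5 × 0.5/50) = 7.1 points. That is not the quantity that reaches the estimate. At ICC 0.1 the generalised least squares weights, summed over the three hospitals of each group, are:

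| Group | T0 | T1 | T2 | T3 |
|---|---|---|---|---|
| 1 | −0.280 | 0.500 | 0.110 | −0.280 |
| 2 | 0 | −0.390 | 0.390 | 0 |
| 3 | 0.280 | −0.110 | −0.500 | 0.280 |

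Each column sums to zero, so a shift common to all hospitals contributes nothing. The rows sum to about 0.05, 0 and −0.05, so stable group differences contribute very little. The squared group weights sum to 1.142; spread over three hospitals per group this is 1.142/3 = 0.381, and √0.381 = 0.617. The exposure-aligned chance shift in share therefore has SD 0.617 × 6.5 = 4.0 points to 0.617 × 7.1 = 4.4 points.

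**4. Resulting distortion (SD = g × SD of shift).**

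- g = 10: 0.4 points
- g = 20: 0.8-0.9 points
- g = 30: 1.2-1.3 points

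**5. Precision gain on a linear scale.** The fraction of variance removed is q(1 − q)g²/0.16, and the SE falls by 1 − √(1 − fraction).

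| g | Variance removed | SE reduction |
|---|---|---|
| 10 | 1.3-1.6% | 0.7-0.8% |
| 20 | 5.3-6.3% | 2.7-3.2% |
| 30 | 11.8-14.1% | 6.1-7.3% |

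**6. Consistency of steps 4 and 5.** At g = 30 and q = 50%, (1.3/3.5)² = 0.14, which is the variance fraction in step 5. So the chance distortion is a component of the SE in step 2, not an addition to it.

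**The case against.** The strongest reply is that nothing here is misstated. The article gives a coherent model with four sensible covariates, another prognostic factor can be proposed for almost any trial, and a fuller analysis plan may already include this one. That stands as a limit on weight. It does not remove the point, because the article names its covariate list and omits the characteristic by which it selects patients.

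Several stronger readings are tempting and are not supported:

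- **A bias of 1-6 points.** This follows if the share differs by 10-20 points between control and intervention cells (0.10 × 0.10 up to 0.20 × 0.30). By chance, 10 points is about 2.3-2.5 SDs of the exposure-aligned shift and 20 points about 4.6-5.0. A shift that large needs real, hospital-specific drift in mix aligned with crossover. The article shows none, and crossover order is randomised.
- **Extra noise on top of the quoted SE.** Step 6 shows that the sampling variation in mix is already counted.
- **Power for the primary outcome falling below 0.85.** At ICC 0.1 it reaches 0.820 only if the share varies between hospital-rounds with an SD of 15 points beyond sampling and the difference between types is 30 points. Nothing in the article supports that combination.
- **Adjusting for a mortality-risk class as well.** The article describes only a threshold of 1%, which every included patient meets. It does not describe a graded class as recorded.

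Two further limits hold. The precision figures are for a linear scale and do not carry over directly to the logistic models. Differences of 10-30 points are also implausible for mortality, for which the Background cites 1.5-3.13%.

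**Conclusion.** The omission is real and worth correcting, but its expected effect on the randomised comparison is small. Under the stated assumptions, chance changes in mix distort the intervention estimate with an SD of about 0.4-1.3 points, contained in an unadjusted SE of 3.4-3.5 points, and adjustment would reduce that SE by about 1-7%. The upper end needs risks as far apart as 5% and 35% at an even mix. Larger bias would require case-mix drift aligned with crossover.

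Of the nine primary indicators, only two are measured per patient (the stop-moment bundle and timing of antibiotic prophylaxis); the other seven are hospital-level and unaffected. The case is strongest for complications, wound infection, ICU transfer, reoperation, readmission and length of stay, and above all for the adherence-outcome association. The size of confounding there cannot be worked out from the article.

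**What to change.** Add type of surgery (abdominal or vascular) as a fixed covariate in all patient-level models, next to age, sex, ASA and SES, and state that the adherence-outcome analysis uses it too. Keep it as this one coarse category for rare outcomes such as mortality.

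The cost is one model degree of freedom among 1,800 patients, plus retaining the procedure type in the study database. The article does not say that it is stored, but it has to be read for every patient to establish eligibility. Trial status reports that no data cleaning or analysis had begun at submission, so on that account the covariate could still be prespecified.

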## Objective

The aim of this study is to investigate the (cost) effectiveness of a multifaceted approach to implement the perioperative safety guidelines. Our main research question isCan we improve the use of the national perioperative safety guidelines at the hospital and patient levels? In other words, does a multifaceted approach to implement the perioperative guidelines lead to a higher compliance than unsupported implementation?Other research questions are the following:Does the perioperative patient safety (i.e., patient outcomes) improve with better adherence to the guidelines?What are the costs of this implementation strategy and what is the cost-effectiveness at the hospital level?What is the feasibility of this implementation strategy at the hospital level?

In this study protocol, we describe a stepped wedge cluster randomized trial design to evaluate the effect of a multifaceted implementation strategy on guideline adherence and patient safety in Dutch hospitals (research questions 1 and 2). We also describe the economic evaluation (research question 3) and process evaluation (research question 4).

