## Methods/design

### Study design

Implementation of Perioperative Safety Guidelines (in Dutch: Implementatie Richtlijnen Operatieve Veiligheid (IMPROVE)) is a multicenter study in nine hospitals using an one-way (unidirectional) cross-over cluster trial design (i.e., the clusters cross over in one direction only, from control to intervention) where each participating cluster receives both intervention and control treatments consecutively, in separate periods.

A stepped wedge design is a sequential roll-out of an intervention (here: the multifaceted implementation strategy) to participants (individuals or clusters of individuals, here: groups of hospitals) over a number of time periods. All groups (hence all hospitals) start with the control situation (no IMPROVE implementation activities) at the beginning of the study. At each time point, a new group of three hospitals crosses over from the control situation to the implementation situation. Good balance of hospital characteristics (e.g., hospital type and geographical location) over the groups (of three hospitals) was achieved by matching. Each group will start the implementation phase of 4 months at a different time point, directly after one of the measurements (T0, T1, T2). The time point a group crosses over is randomized (over the groups). Randomization was computer generated by an independent statistician when recruitment of clusters was complete (Additional file 1). By the end of the study, all groups (hence all hospitals) will have received the IMPROVE implementation strategy. The intervention is never removed once it has been implemented, at least over the course of the trial.

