**Standard package**	
Small-scale educational meetings	Workshop or skills training for perioperative key disciplines including assignments, role playing, own presentations, patient stories or discussion, and problem solving of hypothetical patient situations/case studies. Provided by an opinion leader within the field of patient safety or a highly respected colleague. Based on active participation in small groups: multi- or mono-disciplinary groups (i.e., per discipline, e.g., surgeons and recovery nurses separately). The content is based on the key constraints and the most important obstacles in applying the guidelines for a hospital (based on the results of the audit) and a brainstorming session during the training or pre-handed topics participants find important to discuss.
Audit and feedback	Feedback is based on the indicator measurement(s), structural observation, barrier analysis, and the TCI and HSOPS questionnaires. The feedback consists of a local paper report with the hospital’s own results, benchmarked, and presented in relation to all nine participating hospitals. The hospitals in the intervention phase receive this report shortly after a measurement period. The feedback report is presented and discussed with the key professionals in a meeting.
Structural observation	Observation by a trained expert of the pre-, per-, and postoperative trajectory of one surgical patient (on the ward, operation room, and recovery ward) based on a structured observation list. Feedback is based on the completed observation list. The hospitals receive the feedback immediately afterwards. Also, the structured observation list used is then made available to the hospital. In this way, the hospital is able to perform its own observations of the perioperative process.
Local embedding of the guidelines	Concrete and visible integration into and/or completion of a local protocol and/or checklist, for example, the adaptation of the guidelines in a local protocol; conducting audits (indicator measurements), structural observations, and visitation to monitor the implementation of the guidelines; the use of reminder systems (completing existing checklists based on the guidelines, if possible, new digital checklist may be installed in electronic patient records); decision support and feedback on the implementation of the protocol (using ICT); and incorporation of the guidelines in the clinical pathway, e.g., resignation letter to the general practitioner.

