Patient safety cards	Two patient safety cards (each with six cartoons on the front and explanations on the back) based on the perioperative guidelines, entitled “Help us with your safe surgery” and “Discharge from the hospital” are sent to the patients with an accompanying letter in preparation of the preoperative screening or admission to the hospital.
	Both patient safety cards are offered again to the patients on the preoperative outpatient clinic and on the nursing ward, respectively.
	Medical specialist and nurses discuss the patient safety cards with the patient in order to explicitly invite patients to ask questions and to attend caregivers on parts of the cards during their health-care process.

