### Outcome measures

Several outcomes are measured at the hospital (i.e., the cluster) and the patient levels (Table 3). The primary outcome measure is guideline adherence according to the PSIs as defined in the national indicator set. This set comprises nine indicators on the processes and structures of care [18]. Secondary (patient) outcomes are in-hospital complications (with particular attention to postoperative wound infections) and hospital mortality, as well as length of hospital stay (LoHS), unscheduled transfer to the intensive care unit (ICU), non-elective hospital readmission, and unplanned reoperation, which are derived from a maximum period of 30 days after the initial surgery.

**Table 3 Tab3:** **Methods and instruments for measuring the effects of a multifaceted implementation strategy to implement the Dutch national perioperative safety guidelines**

**Outcome variable**	**Data source (type of measurement)**	**Frequency of measurement and sample size per measurement**	**Moment of measurement**	**Unit of analysis**
**Primary outcome** (guideline adherence measured by an indicator set of nine process and structure indicators)				
Completion of the total STOP bundle (seven separate stop moments in the perioperative care process), % patients	Retrospective patient record review in the hospital information systems	4 (T0 (before), T1, T2, T3 (after) measurement) *N* = 1,800	−3 months, +4 months, +11 months and +18 months	Patient
Availability of a protocol on antibiotic use	Short questionnaire on the underlying items of the structure indicators	4 (T0 (before), T1, T2, T3 (after) measurement) *N* = 1	−3 months, +4 months, +11 months and +18 months	Hospital
Timely administration of antibiotic prophylaxis, % patients	Retrospective patient record review in the hospital information systems	4 (T0 (before), T1, T2, T3 (after) measurement) *N* = 1,800	−3 months, +4 months, +11 months and +18 months	Patient
Availability of a protocol on anticoagulant use	Short questionnaire on the underlying items of the structure indicators	4 (T0 (before), T1, T2, T3 (after) measurement) *N* = 1	−3 months, +4 months, +11 months and +18 months	Hospital
Availability of a protocol on responsibilities regarding maintenance of medical equipment	Short questionnaire on the underlying items of the structure indicators	4 (T0 (before), T1, T2, T3 (after) measurement) *N* = 1	−3 months, +4 months, +11 months and +18 months	Hospital

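### The adherence-outcome association is given a causal question it cannot answer, and the STOP-bundle part may also be open to reverse causation, depending on when the stop moments fall

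*Protocol article*

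**What the plan says.** Research question 2 in the Objective section asks: "Does the perioperative patient safety (i.e., patient outcomes) improve with better adherence to the guidelines". The Analysis section assigns it to an association: "The association between guideline adherence and patient outcomes will also be analyzed to determine whether better adherence leads to better patient outcomes". The Study population section adds that higher-risk operations were selected so that effects of adherence on patient safety could be detected, so this question also shaped eligibility.

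Randomisation concerns something else. Under Study design: "The time point a group crosses over is randomized (over the groups". The Analysis section separately plans a comparison by treatment group: "multilevel linear and logistic regression analysis will be used to compare the outcomes between treatment groups, with age, sex" and further covariates.

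Table 3 lists nine adherence indicators. Seven are measured per hospital (protocols, regulations, registrations). Two are measured per patient: timely antibiotic prophylaxis and "Completion of the total STOP bundle (seven separate stop moments in the perioperative care process), % patients". The seven stop moments are neither listed nor timed.

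On limitations, the Discussion says that power may be too low for the adherence-outcome question. Against confounding it relies on team climate and safety culture, which Table 3 shows are surveyed once, at T0, among professionals.

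**The concern.** Two problems arise, and they differ in how firmly the text supports them.

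The first is established. Patients who receive fully adherent care may differ from those who do not in illness, complexity of the operation, ward or hospital. An association cannot separate these differences from an effect of adherence, yet the plan gives it that task. Surveys of professionals at T0 do not adjust for patient risk. A low-power caveat warns of a missed effect, not of a spurious one.

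The second is conditional. The bundle counts as completed only if every stop moment is done. If one or more fall after surgery, a patient who dies, has a serious complication or goes unplanned to the ICU may never reach them in the usual way. The outcome then produces the non-adherence.

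At stake is the answer to research question 2. A favourable association could be read as proof that adherence improves patient safety when part or all of it comes from confounding or from the way adherence was scored.

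**Working it through.** **The plan's own figures.** The sample size reproduces: 50 × 9 × 4 = 1,800. With the Hussey and Hughes variance, a 15-point increase from 50%, two-sided alpha 0.05 and 50 patients per cell, power is 0.947 (ICC 0.1) to 0.980 (ICC 0.3) if the total variance is 0.25, and 0.925 to 0.920 if the residual variance is 0.25. The stated minimum of 0.85 holds. That calculation concerns the strategy's effect on adherence; the article gives no figure for the adherence-outcome analysis.

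**Could stop moments come after surgery?** The bundle is placed in the perioperative care process. Table 2 describes observation of the "pre-, per-, and postoperative trajectory of one surgical patient (on the ward, operation room, and recovery ward", and patient cards "based on the perioperative guidelines, entitled “Help us with your safe surgery” and “Discharge from the hospital". Complications are defined to include events during treatment as well as after it. Late stop moments are therefore plausible, but no passage says that one exists.

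**Size if they do.** Inputs: N = 1,800 (article); completion c = 50% among patients without an event (the article's assumed baseline level); no effect of adherence on outcome. Let b be the assumed share of event patients, among those who would otherwise complete, whose event blocks completion.

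- Completion among event patients: c(1 − b).
- Odds ratio for an event, complete versus incomplete: [c(1 − b) / (1 − c(1 − b))] ÷ [c / (1 − c)]. With c = 0.5 the divisor is 1.
- b = 10%: 0.45/0.55 = 0.82.
- b = 25%: 0.375/0.625 = 0.60.
- b = 50%: 0.25/0.75 = 0.33.

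The odds ratio does not depend on the event rate. With c = 65% the same shares give 0.76, 0.51 and 0.26.

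**Worked cell, event rate 10% (assumed), b = 25%.** There are 180 events; 180 × 0.375 = 67.5 are completers and 112.5 are not. Of 1,620 patients without an event, 810 are in each group. Event risk is 67.5/877.5 = 7.7% in completers and 112.5/922.5 = 12.2% in non-completers.

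**Chance of P < 0.05 with no true effect** (two-proportion test, 1,800 patients, c = 50%, clustering ignored):

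| Assumed event rate | b = 10% | b = 25% | b = 50% |
|---|---|---|---|
| 3% | 11% | 44% | 95% |
| 10% | 25% | 89% | about 100% |
| 20% | 40% | 99% | about 100% |

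**Confounding alone, for scale.** Assume an unmeasured risk factor with 30% prevalence, a 10% event risk without it, a risk ratio of 1.5 to 3, and lower adherence in those who have it (45% versus 55%, or 40% versus 60%). The odds ratio is then 0.96 to 0.78. If staff were instead more adherent in high-risk patients, this bias would run the other way.

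**The case against.** The strongest reply is that the plan calls the analysis an association, asks an open question, and separately plans a randomised comparison of the same patient outcomes. The defect is therefore confined to one secondary analysis and the purpose written for it. That stands, and it limits the point. It does not remove it, because the stated purpose is causal and no caveat on bias is attached to it.

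The second reply is that the blocking mechanism is not in the document. This also stands: without the timing of the stop moments it can only be put as a condition. The discharge card is an implementation tool, not a stop moment. The mechanism cannot affect the seven hospital-level indicators, hardly affects antibiotic timing, and does not apply to readmission after discharge. With little blocking, or with rare events, a spurious significant result is far from certain.

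Two stronger readings are tempting. A reader might take an extreme case: 3% in-hospital mortality (54 of 1,800), a last stop moment at discharge, and completion by half of the 1,746 survivors. Mortality would then be 0/873 in completers and 54/927 = 5.8% in the rest, as if the definition alone settled the question. The arithmetic is right, but nothing in the article places a stop moment at discharge, and it is a single extreme choice. A reader might also fault the covariate list for omitting type of surgery, or the model for mixing differences between and within hospitals. The article states its covariates and multilevel model for the treatment-group comparison and gives no model for the association, so that criticism has no stated target.

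**Conclusion.** The concern holds in limited form. On the text alone, a causal question is assigned to a comparison of patients whose adherence was not randomised, and the only caveat offered for it is low power. If some stop moments fall after surgery, scoring the whole bundle adds a bias in favour of adherence: an odds ratio of about 0.82 to 0.33 with no true effect, for blocking shares of 10% to 50% and 50% completion. The shares, event rates and confounder strengths are assumptions, because the article gives none for this population. The documents do not support saying that research question 2 would be answered favourably whatever the truth; they support saying that it could be. The primary adherence comparison and its sample size are unaffected.

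**What to change.** - State that the adherence-outcome result will be reported as an association, not as evidence that adherence improves outcomes.
- In that analysis, score STOP-bundle adherence only on stop moments due before the outcome could occur: for example, those before or during the operation, with outcomes counted afterwards. Counting outcomes only from then on matters because complications are defined to include events during treatment.
- Adjust this analysis for measurement round, and for type of surgery where it is recorded.
- Rest any causal statement about patient outcomes on the randomised comparison of strategy with control that is already planned, worded as the effect of the strategy.

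**Cost.** No new patients are needed, and the article reports that neither data cleaning nor analysis had begun. Scoring stop moments separately requires that they were recorded separately, which the all-or-none indicator implies. The claim becomes weaker, and some information from late stop moments is lost. The randomised comparison may also be imprecise. If completing the bundle lowered event risk by 5 to 10 percentage points (assumed), a 15-point rise in adherence would lower it by only 0.15 × 5 = 0.75 to 0.15 × 10 = 1.5 points, which agrees with the article's own warning on power.
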